## Abbreviations

|       |                                                                   |
|-------|-------------------------------------------------------------------|
| AI    | Artificial Intelligence                                           |
| CKPT  | Checkpoint                                                        |
| CNAG  | Centro Nacional de Analisis Genomico                              |
| DBS   | Dried blood spots                                                 |
| DRKS  | German Clinical Trials Register                                   |
| EFPIA | European Federation of Pharmaceutical Industries and Associations |
| EHR   | Electronic Health Records                                         |
| EMA   | European Medicines Agency                                         |
| ERN   | European Reference Network                                        |
| FDA   | Food and Drug Administration                                      |
| gNBS  | Genetic newborn screening                                         |
| HCP   | Health Care Provider                                              |
| HPO   | Human phenotype ontology                                          |
| IMI   | Innovative Medicine Initiative                                    |
| ML    | Machine learning                                                  |
| NBS   | Newborn screening                                                 |
| NGS   | Next generation sequencing                                        |
| OPBG  | Ospedale Pediatrico Bambino Gesù                                  |
| RDs   | Rare diseases                                                     |
| S4C   | Screen4Care                                                       |
| VUS   | Variants of uncertain significance                                |
| WGS   | Whole genome sequencing                                           |
| WP    | Work package                                                      |

## 1 Project summary

This study is part of the EU research project “Screen4Care: Shortening the path to rare disease diagnosis by using newborn genetic screening and digital technologies” ([www.screen4care.eu](http://www.screen4care.eu)) and aims to investigate the use of next generation sequencing (NGS) technologies as part of newborn screening.

In parallel to established national newborn screening programs, we will offer research participants to perform NGS based genetic testing for a predefined number of genetic disorders. We aim to include 18000 participants in 6 participating countries (Italy, Germany, France, Greece, Poland and Czech Republic) . All participants will be tested for a set of TREATable diseases. Gene selection is always based on a predefined set of criteria. The TREAT-panel refers to genetic diseases with onset during childhood, for which there is an established treatment available.

Only pathogenic or likely pathogenic variants will be reported to participating families. Carrier status for monoallelic recessive pathogenic /likely pathogenic variants will be communicated if requested by the couple according to the informed consent. VUS will not be reported. In case of positive findings, full access to clinical examination and confirmatory genetic or metabolic tests will be ensured by the participating birth centers and clinical S4C partners through ERN collaboration. If presence of a genetic rare diseases is confirmed, families will be addressed to the ERN reference centres to initiate appropriate follow-up and treatment.

Families with negative genetic newborn screening tests will regularly be contacted for a follow-up period of at least 12 months. If infants will develop symptoms suggestive of a genetic disease, whole genome sequencing (WGS) of the entire Mendeliome will be freely offered as part of the research project. The WGS study protocol will be part of a separated, dedicated ethical application. Further, a technical validation TREAT-PANEL sub-study (involving a cohort of about additional 200 newborns TREAT-WGS cohort) is planned in Italy and is based on the use of WGS as a “technical validation tool” of the TREAT-panel, to test the accuracy of TREAT panel to identify both small variations and copy number variations (CNVs). In this study the genetic output will remain those of the TREAT panel study, therefore exclusively the 244 genes included in this panel will be “in silico” interrogated in newborns (TREAT-panel “in silico” with WGS backbone). No other information will be provided to the couples and all materials already presented in the TREAT panel study application will remain unchanged. A new informed consent is needed, since the newborn screening method will be WGS and not the TREAT panel.

## 2.5 Duration and financing

The study is funded as part of the Screen4Care project, which will run for a period of 6 years with a total budget of 25 million euro, provided by the IMI 2 JU, a joint undertaking of the European Union (EU) and the European Federation of Pharmaceutical Industries and Associations (EFPIA).

## 2.6 Registration

The study will be registered in ClinicalTrials.gov

# 3 Scientific Background

## 3.1 The Screen4Care project

This research project entitled “Screen4Care: Shortening the path to rare disease diagnosis by using newborn genetic screening and digital technologies” or Screen4Care (S4C), in short is a new EU Research Project and is an international public-private collaboration of 37 partners led by the University of Ferrara and including academic partners, industrial partners, small and medium-sized enterprises partners and EURORDIS. This ambitious project brings together experts with a wide range of expertise, including genetics, data management, ethics, and cybersecurity as well as the rare disease (RD) patient community.

S4C will last for a period of six years with a total budget of EUR 25 million provided by the Innovative Medicines Initiative (IMI 2 JU), a joint undertaking of the European Union and the European Federation of Pharmaceutical Industries and Associations (EFPIA). IMI is Europe's largest public-private initiative aiming to speed the development of better and safer medicines for patients.

In the EU alone, according to the Orphanet database (<https://pubmed.ncbi.nlm.nih.gov/31527858/>), 30 million persons, 3.5-6% of the general population, are affected by one of the 6,172 different rare diseases (RDs) of which 72% are genetic and 70% affect children. The path to diagnosis for people suffering from a RD is burdensome, often severely delayed by a diagnostic odyssey. People living with RDs often find themselves on a burdensome journey to diagnosis, enduring on average of eight years of inconclusive consultations and possible misdiagnoses, leading to ineffective treatments and inefficient healthcare resource utilisation. Lack of timely diagnosis affects disease management, family planning, identification of potential beneficial treatments and / or clinical trials. This unacceptable situation does not meet the concept of equity for EU citizens, and requires rapid, structured, and cost-effective corrective actions. The S4C consortium will leverage the genomic and digital advent to develop and pilot genetic newborn screening (gNBS) and AI-guided symptom recognition algorithms, while accounting for all relevant legal, regulatory and ethical considerations.

The project offers an innovative research approach to significantly shorten the time required for RD diagnosis and efficient intervention, through two central pillars: gNBS and digital technologies.

1. **Genetic newborn screening:** The project will drive newborn screening, using genetic testing and related advanced genomic technologies, which is anticipated to be an effective tool for early diagnosis considering that approximately 72% of RDs have a genetic cause and 70% of RD patients are children. In particular, gNBS, will adopt different strategies interrogating: I) currently treatable RDs (TREAT-panel-approach). In addition, whole genome sequencing (WGS) of the entire Mendeliome will be offered to early symptomatic patients enrolled in gNBS studies to identify known RDs, not included in the gene panel(s) and novel genes/phenotypes. Further, a short technical validation TREAT-PANEL sub-study (involving a cohort of about additional newborns TREAT-WGS cohort) is planned in Italy and is based on the use application of WGS as a “technical validation tool” of the TREAT-panel, to test the accuracy of TREAT panel to identify both small variations and copy number variations. In this study the genetic output will remain those of the TREAT panel study, therefore since exclusively the 244 genes included in this panel will be “in silico” interrogated in newborns (TREAT-panel “in silico” with WGS backbone). No other information will be provided to the couples and all materials already presented in the TREAT panel study application will remain unchanged. A new informed consent is needed, since the newborn screening method will be WGS and not the TREAT panel.
2. **AI-based tools:** The project will design and develop new Artificial Intelligence (AI) algorithms to identify patients at early disease onset via Electronic Health Records (EHR) and develop a repository of AI “symptom checkers” to help patients who are in the midst of their diagnosis journeys – both supporting symptom-based diagnosis later in life. Therefore, S4C aims to use the power of innovative digital solutions to shorten time to diagnosis via two routes: I) predictive

algorithms, leveraging the S4C data (federated) machine learning (ML) environment and embedded EHR systems; II) a repository of AI “symptom checkers”, which will be designed to facilitate self-diagnosis and/or to suggest referral pathways to physicians for diagnostic workup.

In addition, S4C aims to establish a digital infrastructure and ecosystem to engage patients, parents of newborns and caregivers as equal decision-makers in the diagnosis process. This project will allow continuous data collection and information exchange, contributing to the development of next-generation diagnostics and enabling physicians, patients and relatives to make informed decisions at an earlier stage. For a general project overview see **Appendix I (A & B)**.

### 3.2 Genetic newborn screening (gNBS)

Expanded newborn screening is an important public health program aimed to screen all newborns. The role of the programme is secondary prevention aimed to provide early diagnosis and to prevent or ameliorate the long-term consequences of the disease for newborns who are suffering from Inherited Metabolic Disorders (IMDs).

The introduction of tandem mass spectrometry (MS/MS) in NBS offered the possibility of screening for almost 50 conditions using a single dried blood spot (DBS).

In Italy a nationwide newborn screening program for inborn errors of metabolism was institutionalized by law between 2016 and 2017 (Law 167/2016, [https://www.gazzettaufficiale.it/eli/id/2016/08/31/16G00180/sg](https://www.gazzettaufficiale.it/eli/id/2016/08/31/16G00180/sg;); DM 13 October 2016, <https://www.gazzettaufficiale.it/eli/id/2016/11/15/16A08059/sg>; DPCM 12-1-2017, <https://www.gazzettaufficiale.it/eli/id/2017/03/18/17A02015/sg>).

Since 2016, Italy has thus made extended neonatal screening mandatory throughout the country for over 40 health conditions, resulting the top leader in Europe. They are divided into four main categories: aminoacidemias, organic acidemias, urea cycle defects and fatty acid oxidation disorders.

Through advances of genetic testing technologies, it is nowadays also possible to use DNA sequencing from DBS to test for genetic diseases (genetic newborn screening, gNBS). First national screening programs have already integrated genetic testing in newborn screening to detect diseases like cystic fibrosis or spinal muscular atrophy. In parallel, the number of diseases, for which treatments are available are constantly increasing.

In Italy, the “Piano Nazionale Malattie Rare (2023-2026) ([document attached](#)) is a central “planning tool” in the field of rare disease. It is extremely relevant that this document has identified the following among the actions to be undertaken in the field of neonatal screening: “promote the collection of residual biological material from internal neonatal screening biobanks for use for diagnostic and research purposes”.

This study aims to explore the use of more extensive genetic testing to screen newborns for treatable genetic diseases.

In particular, gNBS is one of the pillars and the “core” of WP3 of S4C project; indeed, this work package (WP3) aims at exploring the use of gNBS in newborn as a gateway to shorten the diagnostic path and offer the opportunity for early treatment.

gNBS will adopt different strategies interrogating currently treatable RDs (TREAT-panel-approach); Whole genome sequencing (WGS) of the entire Mendeliome (the list periodically updated of the pathological hereditary conditions) will be offered to symptomatic patients to identify known gNBS-escaped RDs and novel genes/phenotypes. WGS study is described as part of separated, specific ethical applications.

The TREAT panel is the tool which will be used in the current study and will include 244 disease genes that are related to treatable genetic disorders, prioritizing those with early onset and where natural history key elements are known. Other 7 genes are also included in the TREAT-panel. These genes are not disease genes but are technical internal controls we will screen especially to identify copy number variations (namely deletions or duplications) in TREAT genes.

Genes were included in the TREAT-panel only when they fulfilled the following criteria: availability of an early, paediatric treatment, which is typically initiated during the first two years of life, disease onset during childhood, high penetrance, and known genotype-phenotype correlation. The gene/disease selection was a crucial step in gNBS planning and TREAT-panel design, therefore robust criteria and scoring have been applied to design the gene panels. Criteria for disease selection and list of TREAT genes, are listed in **Appendix II**.

Further, a sub-study (involving an additional cohort of 200 newborns, called TREAT-WGS cohort) is planned in Italy and is based on the application of WGS as a “technical validation method” on the TREAT-panel, meaning that exclusively the 244 genes included in the TREAT panel will be interrogated (TREAT-WGS). This TREAT-WGS validation study aims at testing the accuracy and the detection rate of the TREAT panel in the identification of both small variations and copy number variations. In this study the genetic output will remain those of the TREAT panel study, therefore only the 244 genes included in this panel will be interrogated “in silico” in this newborn cohort (TREAT-panel “in silico” on WGS backbone) for both small and copy number variations. No other genetic data will be provided to the couples and all materials already presented in the TREAT panel study application will remain unchanged. A new informed consent is needed, since the newborn screening method will be WGS and not the TREAT panel.

The same information, dissemination, and communicating tools of the TREAT-panel will be adopted: therefore, WGS will be carried out with the sole purpose of validating the technical “accuracy and sensitivity” of the targeted gene panel, allowing a comparison of feasibility, detection rate, and gene coverage (targeted TREAT-panel vs TREAT-panel *in silico* on WGS backbone) in detecting small and copy number variations.

The application of WGS as a “technical validation tool” of the TREAT-panel will provide robustness to the TREAT panel diagnostic grade, for future application and translation into the health system for gNBS, especially for some variants, as copy number variations or structural variants, which may escape the TREAT panel testing. None of the non-TREAT genes genomic output generated by the WGS approach will be disclosed or provided to the couples and no risk of communicating “incidental findings” and “secondary findings” will occur, thus being a substudy fully compliant with the ethical rule of Screen4Care project.

The choice of using targeted sequencing, gene panel and the application of WGS as a “technical validation tool” maximises the screening ability to enrich for interpretable variation, including copy number variations and complex genotypes due to structural variants , provides a more understandable expectation to parents, allows rapid data processing and cost-effective data storage, and avoids many of the complex ethical issues associated with incidental findings and participant privacy inherent in whole exome or whole genome sequencing, being fully adherent to the World Health Organization ethical guidelines for genetic testing (<https://apps.who.int/iris/handle/10665/63910>, 1997). However, when patients present with early symptomatic disease, those who tested negative on the TREAT panel will be offered optional Whole Genome Sequencing (WGS) of the entire Mendeliome to recognize known gNBS-escaped RDs and novel genes/phenotypes.

In addition, communications with European Reference Networks (<https://webgate.ec.europa.eu/ern/>) will help map out post genetic report diagnosis work up and referrals and will ensure full access to positive infants to available therapies.

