## 4 Study goals

### Primary endpoints:

- Percentage of eligible couples who will accept to participate to the TREAT-panel (Cohort TREAT panel)
- Percentage of eligible couples who will accept to participate to the TREAT-panel in silico with WGS backbone (Cohort TREAT-WGS)
- Percentage of study participants in whom a pathogenic or likely pathogenic variant in appropriate inheritance model will be identified through TREAT-panel
- Percentage of study participants in whom a pathogenic or likely pathogenic variant in appropriate inheritance model will be identified through TREAT- WGS
- Percentage of study participants resulted fully negative at the gNBS (through both TREAT-panel and TREAT- WGS)

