**Important Note:**

The couples' choice to participate to the two different cohorts' studies (TREAT-panel and TREAT-WGS) will be free, recruitment will be competitive in both cohorts, meaning that when reached the established number of infants to be screened (200 for TREAT-WGS, and 18.000 for the TREAT panel) the recruitment will be closed for both cohorts.

A schematic representation of gNBS pipeline is reported in **Appendix IV**.

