## 6 Methods and realisation

### 6.1 Sample collection and analysis

Samples will be collected on the dedicated S4C DBS card in parallel with the collection of the DBS card of the metabolic newborn screening. Then samples will be pseudonymized at S4C birth centres and shipped to OPBG Hub, for DNA extraction and TREAT-panel NGS sequencing.

For a list of genes screened by panel for TREATable diseases see **Appendix V**.

Extracted DNA from S4C DBS cards will be conserved as pseudonymized at the OPBG hospital for the entire S4C duration, as described in Deliverables. OPBG will be responsible partner for sample conservation. If specified and agreed in the informed consent, S4C DNAs can be used for research purpose only for future S4C activities only, in their strictly anonymized habit. In some (expected a few) cases of cohort TREAT-WGS, when DNA quality extracted from the DBS might not be adequate, a

newborn peripheral blood sample taken might be needed and requested to the couple, as clearly mentioned in the informed consent.

The OPBG Hub will transmit by a dedicated, encrypted cloud platform BaseSpace (the S4C data repository, described in WP2) the raw data of gNBS sequencing output. Data will be therefore analyzed by two different partners: CNAG (Centro Nacional de Analisis Genomico) in Barcelona and Genoox in Tel Aviv, which will have access to this platform and are fully committed to be adherent to the ethical and confidentiality rules of S4C, as described in Deliverable D6.11 ([document attached](#)).

Results will be available to consortium members and through the RD-Connect GPAP and Genoox/CNAG platforms (whose access is limited to S4C consortium partners only and double-checked). These will make the data FAIR-field and sharable within the project in a privacy-preserving and controlled data access environment. As the aim of the TREAT-panel is to identify diseases where early diagnosis and treatment might benefit the health of the affected infant, the scientific report (prepared and finalized by CNAG and GENOOX) will report all variants identified in the TREAT genes. This report will be delivered to S4C validation Hubs (OPBG, UNIFE and Freiburg) that will perform variants' evaluation ("manual curation") and eventually a technical validation of the identified variants.

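### The TREAT-WGS sub-study cannot estimate the panel's accuracy or sensitivity, because no infant is described as having both assays

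*Protocol*

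**What the plan says.** Section 3.2 states the purpose twice. First: "This TREAT-WGS validation study aims at testing the accuracy and the detection rate of the TREAT panel", for small variants and for copy number variants (CNVs). Then: "WGS will be carried out with the sole purpose of validating the technical “accuracy and sensitivity” of the targeted gene panel". Sections 1 and 3.1 also describe WGS as a technical validation tool that tests the panel's accuracy. Section 3.2 expects the result to strengthen the panel's diagnostic standing, and Section 7.2 cites the sub-study in response to the risk of falsely negative panel results.

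Section 3.2 describes the cohort as a sub-study "involving an additional cohort of 200 newborns, called TREAT-WGS cohort", and on the test used it says: "A new informed consent is needed, since the newborn screening method will be WGS and not the TREAT panel". The 244 panel genes are read in silico from the WGS data. The Important Note in Section 5.3 treats the two groups as different cohorts between which couples choose freely, with separate targets: "the established number of infants to be screened (200 for TREAT-WGS, and 18.000 for the TREAT panel".

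Section 4 lists the endpoints. Those that involve TREAT-WGS are acceptance, yield, a technical assessment of TREAT-WGS, and comparisons between the methods on feasibility, detection rate, gene coverage, and number and type of variants. Section 6.1 adds that for some TREAT-WGS infants with poor dried blood spot (DBS) DNA a "newborn peripheral blood sample taken might be needed and requested to the couple, as clearly mentioned in the informed consent".

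**The concern.** Sensitivity is the share of variants truly present in a sample that the panel calls in that same sample. Accuracy likewise needs a reference result for each panel result. If WGS is the reference, it has to be run on samples that the panel has also read. The design instead gives WGS to one set of infants and the panel to another, so the aim and the design do not fit together.

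The variants of most interest here are the CNVs and structural variants that Section 3.2 says may escape the panel. A variant that the panel misses in a panel infant stays invisible, because that infant has no WGS. A variant that WGS finds in a WGS infant says nothing about whether the panel would have missed it. The sub-study could be completed exactly as planned and still provide no evidence for its stated purpose. A later analysis plan cannot repair this, because the paired data would not exist.

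**Working it through.** **1. Can sensitivity be formed?**

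| Needed | Described in the protocol |
|---|---|
| Panel result and WGS result on the same infant | WGS infants: WGS and not the panel (Sections 1, 3.1, 3.2) |
| A subset of panel infants with WGS as reference | None; separate cohorts and targets (Section 5.3) |
| Verification of panel negatives | Only WGS of infants who develop symptoms, under a separate application (Sections 1, 6.2) |
| Verification of panel positives | Technical validation of variants already called (Section 6.1) |

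Paired infants described: 0. True-positive, false-negative and concordance counts for the panel cannot be built. Technical validation looks only at calls already made, so it cannot show what was missed. WGS of symptomatic infants covers a selected group.

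**2. What does the unpaired comparison give?** The protocol states no precision target or other basis for the 200, so there is no figure to reproduce. The inputs are about 500 positives (Section 6.1) among 18,000 + 200 = 18,200 infants.

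- Expected rate: 500 / 18,200 = 2.75%.
- Expected positives in TREAT-WGS: 200 × 0.0275 = 5.5 (95% binomial range 1 to 10).
- Expected positives in the panel cohort: 18,000 × 0.0275 = 495.
- Exact (Clopper-Pearson) 95% CI: 5/200 gives 0.8% to 5.7%; 6/200 gives 1.1% to 6.4%.
- Panel/WGS rate ratio with 5/200: (495/18,000) / (5/200) = 0.0275 / 0.025 = 1.10. SE of the log ratio = √(1/495 − 1/18,000 + 1/5 − 1/200) = 0.444. The 95% CI is 1.10 × exp(±1.96 × 0.444) = 0.46 to 2.63.

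Nearly all of that variance comes from the term 1/5, the WGS positives, so the size of the panel cohort hardly matters. The interval would fit a panel that finds under half of what WGS finds, and equally one that finds more than twice as much.

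**3. What would pairing the 200 give?** If the panel detects all k WGS-positive infants, the exact two-sided 95% lower bound for sensitivity is 0.025^(1/k).

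| k detected of k | Lower bound |
|---|---|
| 5/5 | 48% |
| 6/6 | 54% |
| 10/10 | 69% |

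Ten is the ceiling implied by the expectation in Sections 6.1 and 6.2 that over 95% are negative: 200 × 0.05 = 10. Section 7.1 quotes an accuracy grade of 97% without defining it. If that were read as participant-level sensitivity (my assumption), a lower bound of 97% with no misses needs ln(0.025)/ln(0.97), rounded up to 122 positives. That is about 122 / 0.0275 ≈ 4,440 paired infants. Pairing 200 infants therefore makes accuracy estimable, but useful precision is likely only per variant, over all calls in the 244 genes. The protocol gives no expected count of those calls, or of CNVs.

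**The case against.** The strongest reply is that the sub-study is useful without pairing. The sentence that names the sole purpose goes on to mention feasibility, detection rate and gene coverage. No endpoint in Section 4 is labelled sensitivity or accuracy, and every listed one can be described in separate cohorts. This stands. The defect lies in the stated aim and the claims built on it; no endpoint becomes incomputable.

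It can also be said that pairing may exist somewhere unseen. The pipeline figure in Appendix IV is not shown, annex D6.13 is not at hand, Section 5.2 lists both consents, and Section 6.1 mentions panel sequencing for samples generally. This limits certainty about intent, but Sections 1, 3.1, 3.2 and 5.3 agree with one another. Section 5.2 read literally would require both consents from everyone. If double testing is intended, the text still needs correcting.

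Four stronger readings go beyond the documents:

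- A reader might infer that the last primary endpoint, "Percentage of study participants resulted fully negative at the gNBS (through both TREAT-panel and TREAT- WGS"), requires infants tested twice. Section 4 uses the same phrase for all positive infants who are to be referred, where it can only mean pooled over the two cohorts.
- A reader might infer that the sub-study fails for lack of power to show a difference in detection rates. Section 8 calls the analysis mainly descriptive and promises no such test, so only interval widths are used above.
- A reader might infer that an Italian WGS cohort and a six-country panel cohort cannot be compared fairly. The appendix on expected cases refers to 14,000 infants screened in Italy, so an Italian comparator can be used. The free choice of cohort applies to both groups, and the documents do not link it to yield.
- A reader might infer that peripheral re-draws favour WGS. Section 6.1 expects only a few, and a re-draw can equally be counted against WGS feasibility. Separate reporting is enough.

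**Conclusion.** The point holds. As written, the sub-study has no paired infants and cannot estimate the panel's sensitivity or accuracy, for small variants or for CNVs. What remains is an unpaired description, with about 5.5 expected positives and an interval of roughly 0.8% to 5.7% around the WGS yield. This does not make the sub-study worthless: acceptance, feasibility, coverage, and number and type of variants can still be reported.

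The figures take the plan's 500 in 18,200 at face value and assume the same yield in both cohorts. The conclusion about sensitivity needs neither assumption. It rests only on the protocol's description of separate cohorts with one test each.

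**What to change.** Choose one route before TREAT-WGS recruitment proceeds, and align Sections 1, 3.1, 3.2, 4 and 7.2 with it.

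**(a) Pair the assays.** Run the panel and WGS on the same 200 Italian infants, counted within the 18,000 and with consent to both. Report per-variant positive and negative agreement with exact CIs, separately for small variants and CNVs. State in advance that participant-level sensitivity will stay imprecise (5/5 detected has a lower bound of 48%) and that few CNVs may be seen.

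Cost: a protocol amendment, a combined consent, and about 200 fewer distinct infants (200 / 18,200 = 1.1%). No extra sequencing runs are needed, since 200 WGS and 18,000 panel runs are already planned. The protocol does not say whether one DBS card yields enough DNA for both assays, so this must be checked first.

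**(b) Restate the aim.** Delete the claims that the sub-study tests the panel's accuracy and sensitivity and that it strengthens the panel's diagnostic standing. Call it an unpaired description of coverage, feasibility, yield and acceptance, compared with Italian panel infants. The cost is wording only. This is a full alternative to (a), at the price of leaving the panel's accuracy unmeasured.

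**Under either route,** report coverage and feasibility on the first DBS extraction, and show infants re-drawn as peripheral blood separately.
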